#### 3.8.2. Intervention Group

Pregnant women in the intervention group will receive dietary intervention designed based on BCW, including an individual primary consultation at enrollment, two additional consultations at reviews, and online consultations. Each essential condition in COM-B system often corresponds to multiple intervention functions, policies, and behavioral change techniques (BCTs). Therefore, researchers will select intervention components according to APEASE criteria (affordable, practical, efficacious, acceptable, safe, and equitable) in this study [25]. The matrix of links between the components of BCW (COM-B system, intervention functions, and policy category) for the intervention is described in Table 1.

In the individual primary consultation at enrollment, four intervention strategies will be implemented: (1) Determining the positive and adverse aspects of pregnant women’s current dietary behaviors, and emphasizing the benefits of positive behaviors and the consequences of adverse behaviors, (2) clarifying the importance and principles of dietary control for the treatment of GDM and helping pregnant women to set goals for glycemic control, (3) providing the same guidance materials and explaining the content of the paper guidance materials as the control group for designing daily recipes, showing the additional food atlas showing the shape, volume ration and energy value of food under different grams, different dry and wet states and different cooking methods, and providing the same type of simple food scales to pregnant women for determining the amount of food intake, training pregnant women to design the daily recipes.

In the online consultation at three days after enrollment, three intervention strategies will be implemented: (1) Evaluating the dietary behaviors of pregnant women in the past three days and correcting the wrong dietary behaviors as the control group, (2) informing pregnant women’s main caregivers about the importance of dietary control for women with GDM and the benefits of providing good family support, i.e., enhance pregnant women’s motivation to comply with dietary control, (3) putting forward some suggestions on how to control the diet when participating in a multi-person dinner. For example, use a spoon to estimate the intake amount of a certain food. In the online consultation at 7:00 pm every Friday, two intervention strategies will be implemented: (1) Providing the same online guidance team to answer pregnant women’s questions and conduct health education in the WeChat communication group as the control group, (2) helping pregnant women to design recipes for the next week’s diet.

In the first additional consultation in one week after enrollment, two intervention strategies will be implemented: (1) Deciding the next phase of treatment for pregnant women according to the reexamination results of maternal glucose metabolism, just as researchers do for the control group, (2) setting up the collaborative dietary management group of three women with GDM and encourage them to share dietary control experience, so as to achieve peer education and model setting.

In the second additional consultation at 28 weeks of gestation, researchers will instruct pregnant women to increase 450 kcal on their daily basal energy requirements calculated from their pre-pregnancy BMI and body energy coefficient [32], so as to properly adjust exchange servings of a certain food.

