### 3.5. Sample Size

Due to the lack of prior data about applying BCW in dietary intervention in women with GDM, a pilot study will be carried out to provide a comprehensive estimate of the effect size of the intervention. The recruitment goal of the pilot study is 30 pregnant women with GDM for each group [29]. No a priori hypotheses of effect size to identify the ineffectiveness of a comprehensive study were proposed since we considered that the available data were insufficient to create these meaningfully. The minimum sample size for the future study will be calculated based on the results of the pilot study.

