### 3.7. Randomization and Blinding

Researchers will use the study website (www.random.org/lists/, (accessed on 19 May 2022)) to create random numbers that correlate to the serial numbers before recruiting participants. The ratio of random allocation is 1:1. Eligible participants will be sequentially recruited and assigned the predetermined random number. Participants with a random number of 1–30 will be divided into the dietary intervention group based on BCW (intervention group), while those with a random number of 31–60 will be divided into the general dietary management group (control group). In this study, participants and interveners will inevitably know the content of the intervention. Therefore, researchers will only ensure the separation of interveners and result assessors.

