## 6. Statistical Analysis

All quantitative analysis will be conducted through IBM SPSS Statistics 24.0 software (IBM Corp. Released 2016. IBM SPSS Statistics for Windows, Version 24.0., IBM Corp.: Armonk, NY, USA). The baseline characteristics of participants will be presented by descriptive statistics. The continuous variables will be described by means and standard deviation, or medians and quartiles. The frequencies (N) and percentages (%) will be used for categorical variables. The analysis of variance (ANOVA), Kruskal–Wallis, test or Chi-square test will be used to describe the mean differences of continuous variables and categorical variables between the two groups at baseline. The explored assessment will be analyzed by repeated measures multivariate analysis of variance (MANOVA), and then the post-hoc pairwise comparison will be made. Effect sizes were calculated with Cohen’s d. P value of 0.05 will be considered the significant level for all outcomes.

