The first additional consultation at review	At one week after enrollment	Pregnant women	Communication; Guideline; Service provision;	*Persuasion, incentivization, and enablement*: Re-measure blood glucose, and look back and analyze the dietary-related reasons for the positive or reverse results of controlling blood glucose	√	√	√	√	√	√
			Communication;	*Education, persuasion, and modeling*: Set up the three-person cooperation group to achieve peer education		√	√		√	√
The second additional consultation at review	At 28 weeks of gestation	Pregnant women	Communication;	*Education*: Recalculate total daily energy requirements, and adjust exchange servings of a certain food for meeting the need for the healthy pregnancy		√			√	

**Table 2 ijerph-19-10726-t002:** Timeliness of Data Collection.

	Enrollment	A Week after Enrollment	28 Weeks of Gestation	37 Weeks of Gestation	After Intervention (Before Delivery)	After Delivery

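### Intervention women join three-person peer groups, but the named MANOVA treats all women as independent; if outcomes correlate within triads, the standard error is too small

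*Protocol article*

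**What the plan says.** Women are randomized individually: "The ratio of random allocation is 1:1" (section 3.7), and "The recruitment goal of the pilot study is 30 pregnant women with GDM for each group" (section 3.5).

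One week after enrollment, section 3.8.2 adds for the intervention arm "setting up the collaborative dietary management group of three women with GDM and encourage them to share dietary control experience". The stated aim is peer education and model setting. Table 1 lists the same component under the first additional consultation: "Set up the three-person cooperation group to achieve peer education". Section 3.8.1, on the control group, describes no peer groups of this kind.

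For the outcomes, section 6 says: "The explored assessment will be analyzed by repeated measures multivariate analysis of variance (MANOVA), and then the post-hoc pairwise comparison will be made". It adds: "P value of 0.05 will be considered the significant level for all outcomes". It mentions no peer-group term.

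The data have a second use. Section 3.5 says: "The minimum sample size for the future study will be calculated based on the results of the pilot study".

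**The concern.** The triads are meant to let women influence one another's dietary behavior, and the primary outcomes in section 4 are dietary self-management, dietary self-efficacy and average daily GL. Diagnosis is at 24 weeks. Table 2 places the primary outcome assessments at 28 and 37 weeks, so the triads would normally exist by then. Outcomes of women in the same triad may therefore be correlated, in one arm only. This is a partially nested design.

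A repeated measures MANOVA allows for correlation between measurements on the same woman. It does not allow for correlation between women. Positive correlation within triads would make the variance of the intervention-arm mean larger than the analysis assumes. P values would be too small, and the effect size from the pilot would look more precise than it is. If triad membership is not recorded, the pilot also cannot inform the clustering allowance in the next trial's sample size.

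**Working it through.** **Inputs from the document**
- 30 women per arm (section 3.5), individual 1:1 randomization (section 3.7)
- Group size m = 3, intervention arm only (section 3.8.2, Table 1)
- Significance level 0.05 (section 6)

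**Assumptions**
- Two-sided test (the document does not state sidedness).
- All 30 intervention women are grouped, giving 30/3 = 10 triads.
- Controls are independent of one another.
- Total variance σ² is equal in the two arms.
- ICC between 0 and 0.30, because the document gives none.
- A two-sample comparison at one time point stands in for the between-arm contrast of the MANOVA.

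**Variance of the arm difference**
- Intervention mean: (σ²/30) × [1 + (3 − 1) × ICC] = (σ²/30)(1 + 2·ICC)
- Control mean: σ²/30
- True variance of the difference: (σ²/30)(2 + 2·ICC) = (2σ²/30)(1 + ICC)
- Variance assuming independence: 2σ²/30
- Variance ratio: 1 + ICC, so true SE / naive SE = sqrt(1 + ICC)

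**Type I error of the naive test**: α = 2 × [1 − Φ(1.96 / sqrt(1 + ICC))]. This was checked against 200,000 simulated trials per ICC using an ordinary t-test. The last column is a comparison of triad means with individual controls, with Satterthwaite degrees of freedom, in the same simulated trials.

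| Assumed ICC | True/naive SE | α, closed form | α, simulated naive | α, triad means |
|---|---|---|---|---|
| 0 | 1.000 | 0.0500 | 0.0496 | 0.0491 |
| 0.05 | 1.025 | 0.0558 | 0.0557 | 0.0498 |
| 0.10 | 1.049 | 0.0617 | 0.0623 | 0.0497 |
| 0.20 | 1.095 | 0.0736 | 0.0744 | 0.0502 |
| 0.30 | 1.140 | 0.0856 | 0.0873 | 0.0502 |

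The first row reproduces the plan's 0.05 under independence. Accounting for the triads keeps the error at about 0.05 throughout.

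**Effective size of the intervention arm**: 30/(1 + 2·ICC).
- ICC 0.05: 30/1.10 = 27.3
- ICC 0.10: 30/1.20 = 25.0
- ICC 0.20: 30/1.40 = 21.4

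**Next trial, if it keeps triads in one arm**: the required number is multiplied by 1 + ICC, so 5%, 10% and 20% more women at ICC 0.05, 0.10 and 0.20. Seen from the other side, a size computed without clustering falls short by ICC/(1 + ICC):
- 0.05/1.05 = 4.8%
- 0.10/1.10 = 9.1%
- 0.20/1.20 = 16.7%

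**The case against.** **The inflation is not certain.** A reader might infer that the standard errors are definitely too small and that type I error definitely exceeds 0.05. The document gives no ICC, and at ICC 0 neither is true. If the intervention changed no woman's outcome at all, peer contact could not create correlation either. Inflation would then need peer influence that leaves the mean unchanged, or correlation from the way triads are formed. This stands, so the point is conditional.

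**The intervention is not delivered in groups of three.** A reader might take it that way. The triad is one of about ten strategies in Table 1, the primary consultation is individual, and no triad-led sessions are described. Nor does the text say how women are grouped or that all 30 are. Both arms also have a WeChat group with weekly education, so independent controls are an assumption too. This stands: the triad is one component, and 10 triads is an inference.

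**The effect is small, and this is a pilot.** At ICC 0.05 to 0.10 the true standard error is only 2.5% to 4.9% above the naive one, and the point estimate is unbiased. Testing three primary outcomes, each at 0.05, can already take the familywise rate to about 0.14 (1 − 0.95³). This limits the weight of the point. It does not remove it, because all outcomes are tested at 0.05 and the results feed the next sample size.

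**The pilot cannot estimate the ICC well.** With 10 triads and a true ICC of 0.10, simulation gave a median 95% interval of about −0.22 to 0.55, and a non-negative variance estimate was zero in 34% of trials. This stands and changes the remedy: the estimate cannot set the next sample size alone.

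**A separate analysis plan could add the adjustment.** It could, but the method that the article names does not contain it, and triad membership has to be recorded while the trial runs. Nor does section 3.5 say that the future calculation will ignore clustering, so an undersized next trial is a risk and not a stated plan.

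**Conclusion.** The concern holds in conditional form. The design nests intervention women, but not controls, in peer triads, and the named MANOVA does not allow for it. If outcomes correlate within triads, the true standard error of the arm difference exceeds the naive one by a factor of sqrt(1 + ICC). Over an assumed ICC of 0.05 to 0.20, that is 2.5% to 9.5% in the standard error and a type I error of about 0.056 to 0.074 in place of 0.05. At ICC 0 nothing is lost.

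These sizes rest on all 30 intervention women being grouped, independent controls, equal total variances and ICC values that are not in the document. This is a modest mismatch that is cheap to repair. It does not invalidate the trial.

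**What to change.** 1. Record a triad number for every intervention woman, from the day her group is set up.
2. In section 6, for continuous outcomes, replace the MANOVA with a partially nested mixed model: a random triad effect in the intervention arm only (each control is her own cluster), arm-specific residual variances and Satterthwaite degrees of freedom. Where an outcome is measured more than once, keep the within-woman correlation in the model. The mixed-model procedure of the software already named can do this. An equivalent simpler option is to compare triad means with individual controls, again with Satterthwaite degrees of freedom.
3. Report the triad ICC with its confidence interval.
4. In section 3.5, say that the full trial, if it keeps the triads, will be sized over a range of ICC values and not on the pilot estimate alone.

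The cost is one extra recorded variable and a few sentences of text. Intervals become slightly wider, and the ICC will be imprecise. A version of the model with the triad variance held non-negative was mildly conservative in simulation, with type I error of 0.040 to 0.050.

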## 4. Measures

Primary outcomes for compliance with dietary recommendations include self-management behaviors and self-efficacy of dietary control, and the average daily GL value. Secondary outcomes for maternal glucose metabolism include results of OGTT, FBG, 2 h PBG, and HbA1c. Secondary outcomes for adverse pregnancy outcomes include non-normal gestational weight gain (GWG) (excessive GWG or insufficient GWG), insulin use during pregnancy, cesarean section, premature delivery, macrosomia, and fetal intrauterine growth restriction. The timeliness of data collection is shown in Table 2.

### 4.1. Body Measurement

The height and weight of pregnant women will be measured to calculate pre-pregnancy BMI and gestational weight gain. Pregnant women’s height and weight will be measured via a height and weight measuring instrument, and the results will be accurate to one decimal place.

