### 3.2. Research Setting and Participant Eligibility Criteria

The study will be conducted in the obstetric clinic of a Grade 3A hospital in Wuhan, Hubei Province. Pregnant women diagnosed with GDM by a clinical 75 g oral glucose tolerance test (OGTT) at 24 weeks of gestation are eligible to participate. The glucose concentration thresholds of pregnant women accord with IADPSG criteria in 2010 [28]: Fasting blood glucose (FBG) ≥ 5.1 mmol/L and/or 1-h plasma glucose after taking sugar ≥ 10.0 mmol/L and/or 2-h plasma glucose after taking sugar ≥ 8.5 mmol/L. Furthermore, women with GDM who are eligible must meet the following inclusion criteria: (1) Aged between 18 and 40 years, (2) natural pregnancy, (3) singleton pregnancy verified by ultrasound, (4) have adequate cognitive and behavioral abilities, (5) no previous endocrine-related diseases, such as hyperthyroidism, hypothyroidism, and Cushing’s syndrome, (6) voluntarily participate in this study and sign the informed consent form.

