### 3.6. Recruitment

Participants will be recruited when pregnant women return to the obstetrics clinic for their 75 g OGTT results. Obstetricians will explain the purpose and significance of this study and emphasize that the trial will be conducted in strict confidentiality. Women with GDM who volunteer to participate in this study will be enrolled immediately after signing the informed consent forms.

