### 4.2. Baseline Characteristics Measurement

The baseline characteristics of pregnant women will be measured through the self-designed demographic and pregnancy-related questionnaires, including gestational age, occupation, education level, income, residence place, previous history of disease, gestational weeks, fetal number, existing pregnancy complications, previous pregnancy comorbidities, history of smoking, alcohol abuse and drug abuse, and information about special diet.

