**Body Characteristics**						
Weight	√				√	
Height	√					

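### Section 4.1 derives pre-pregnancy BMI and gestational weight gain from measured weight, but no pre-pregnancy weight is scheduled and Section 4.5 names a different source for weight gain

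*Protocol article*

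**What the plan says.** All references are to the protocol article.

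- **Section 4.1, purpose:** "The height and weight of pregnant women will be measured to calculate pre-pregnancy BMI and gestational weight gain".
- **Section 4.1, method:** "Pregnant women’s height and weight will be measured via a height and weight measuring instrument", with results recorded to one decimal place. This describes a weight taken on an instrument, not one recalled or copied from a record.
- **Table 2, block "Body Characteristics":** weight is ticked twice, at enrollment and after the intervention before delivery. Height is ticked once, at enrollment.
- **Section 3.2:** "Pregnant women diagnosed with GDM by a clinical 75 g oral glucose tolerance test (OGTT) at 24 weeks of gestation are eligible to participate".
- **Section 3.6:** "Participants will be recruited when pregnant women return to the obstetrics clinic for their 75 g OGTT results". Enrollment is therefore at 24 weeks or later.
- **Section 4.2:** the baseline questionnaire is described as "including gestational age, occupation, education level, income, residence place, previous history of disease, gestational weeks, fetal number, existing pregnancy complications, previous pregnancy comorbidities", followed by substance-use history and special diet. Pre-pregnancy weight is not listed.
- **Section 4:** "Secondary outcomes for adverse pregnancy outcomes include non-normal gestational weight gain (GWG) (excessive GWG or insufficient GWG", so weight gain is a secondary outcome and is classified in both directions.
- **Section 4.5:** information on the adverse outcomes, including the two weight-gain categories, is to come from prenatal and delivery records. No pre-pregnancy weight is named there.
- **Section 3.8:** the guidebook is said to hold the method for pre-pregnancy BMI, with reference to Supplementary Files S1 and S2, which are not shown. Sections 3.8.1 and 3.8.2 use pre-pregnancy BMI in the daily energy calculation for both arms.

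**The concern.** A weight first taken at 24 weeks or later already contains the gain of the first and much of the second trimester. It cannot yield a pre-pregnancy BMI. The difference between the two weights in Table 2 is gain since enrollment, not gain over the pregnancy. The measurements that 4.1 and Table 2 describe therefore do not give the two quantities that 4.1 says they will give.

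Three things are at stake.

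1. The outcome of excessive or insufficient GWG could be scored on a partial gain. If the limits depend on BMI class, it could also be judged against the wrong class.
2. Section 3.5 plans to size the future study from this pilot, so distorted event rates could be carried forward.
3. Pre-pregnancy BMI also enters the energy calculation in both arms, so an unclear source affects more than one part of the protocol.

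**Working it through.** The plan gives no figure to reproduce. The check compares the sections and then illustrates the size of the error.

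**Step 1: which weights are available under 4.1 and Table 2?** There are two: W1 at enrollment (24 weeks or later, from 3.2 and 3.6) and W2 before delivery. The weight before pregnancy, W0, is not in 4.1, the items listed in 4.2 or Table 2.

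**Step 2: what is needed?**
- Pre-pregnancy BMI = W0 / height²
- GWG = W2 − W0

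**Step 3: what does the literal reading give?** Let g = W1 − W0 be the gain before enrollment.
- Computed BMI = W1 / height², so the error is + g / height².
- Computed gain = W2 − W1, so the error is − g.

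For any g above zero, BMI is too high and GWG too low.

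**Step 4: size.** The documents give neither g nor height. Assume height 1.60 m (height² = 2.56 m²) and g from 2 to 9 kg.

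| g (assumed, kg) | BMI error, g / 2.56 (kg/m²) | A true BMI of 22 is computed as | An assumed total gain of 12.5 kg is recorded as |
|---|---|---|---|
| 2 | 0.8 | 22.8 | 10.5 kg |
| 4 | 1.6 | 23.6 | 8.5 kg |
| 6 | 2.3 | 24.3 | 6.5 kg |
| 8 | 3.1 | 25.1 | 4.5 kg |
| 9 | 3.5 | 25.5 | 3.5 kg |

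The share of the 12.5 kg that goes unrecorded runs from 2 / 12.5 = 16% to 9 / 12.5 = 72%. If enrollment is at exactly 24 weeks and delivery at 40 (both assumed), the two weights span 40 − 24 = 16 weeks.

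**Step 5: what happens to the classification?** A smaller recorded gain moves women from excessive towards normal, or from normal towards insufficient. An inflated BMI may also change the reference range. The protocol article states neither weight-gain limits nor BMI classes, so the net change in event rates cannot be calculated.

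**Step 6: do the arms differ?** W1 is taken at enrollment, before the programme can act. Under randomization g should be similar in the two arms. The main damage is to the meaning and the event rates of the outcome, not to the direction of the comparison.

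**Step 7: is there another stated source?** Yes, in part. Section 4.5 names prenatal and delivery records for the weight-gain categories. This does not agree with 4.1, which says GWG is calculated from measured weight, and 4.5 does not say which recorded weight is the starting point.

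**The case against.** A reader might infer that BMI will be overstated and GWG misclassified as a matter of fact. The documents do not support that.

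- **Section 4.5 points to records.** It is the section on pregnancy outcomes, and prenatal records may well hold a first-visit or pre-pregnancy weight. No section defines GWG as the difference of the two Table 2 weights. This stands, and it turns the point into a conflict between sections rather than a proven error. It does not remove the point, because 4.1 still states a different method.
- **Supplementary Files S1 and S2 are not shown.** They may base pre-pregnancy BMI on a recalled weight. One therefore cannot say that an inflated BMI enters the energy calculation. This also stands. Section 3.8 cites those files for a method given to participants, however, and does not replace the measurement statement in 4.1.
- **Silence is weak evidence.** Table 2 as shown has no rows for the other record-based outcomes, such as cesarean section or macrosomia, and the list in 4.2 may not be complete. An article also condenses. This is fair for a missing item, but 4.1 is not silent: it names instrument-measured weight as the basis of both quantities.
- **The importance is limited.** GWG is one of several secondary outcomes in a pilot of 30 women per group, the size of the error rests on assumed gains, and the error should be similar between arms. This stands and lowers the severity.

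**Conclusion.** The point holds as a conflict on source. The method in 4.1, combined with the weights in Table 2, cannot produce a pre-pregnancy BMI or a GWG, and 4.5 gives another source for the latter without naming the starting weight. Taken literally, 4.1 overstates BMI by about 0.8–3.5 kg/m² and understates GWG by 2–9 kg. This assumes 2–9 kg gained before enrollment and a height of 1.60 m; the direction needs only that some weight was gained. Whether staff would in practice use the enrollment weight is not established. Bias between the arms is not shown and not expected. Severity is moderate: a secondary outcome in a pilot, but a stated rule that does not work and is easily put right.

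**What to change.** 1. Add a pre-pregnancy weight (or first-visit weight, labelled as such) to 4.1, 4.2 and Table 2. Take it from the prenatal records that 4.5 already uses, with self-report as back-up, and record which source was used for each woman.
2. Define GWG as the last weight before delivery minus that weight, classified by the BMI which that weight gives. Make 4.1 and 4.5 say the same thing.
3. If no such weight can be obtained, relabel the outcome as weight gain from enrollment to delivery and do not call it gestational weight gain.
4. Reconcile the passages in 3.8, 3.8.1 and 3.8.2 that use pre-pregnancy BMI for the energy calculation with the same stated source.

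The cost is one data field and a few changes of wording. The small downside is that a recalled weight carries some error, and a first-visit weight may already include some early gain.
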